### Primary outcome measurement

OSDI will be used as the primary outcome variable. This questionnaire is a 12-item instrument for assessment of ocular irritation and impact on visual function in dry eye sufferers. It can provide quantifiable results of dry eye symptom frequency and vision-related functioning [16]. Each question will be answered on a scale of 0 to 4, where 0 means none of the time; 1, some of the time; 2, half of the time; 3, most of the time; and 4, all of the time. Each patient's OSDI score will be calculated on the basis of the following formula: OSDI = [(sum of scores for all questions answered)*100]/[(total number of questions answered)*4]. We will use the Korean version of the OSDI questionnaire [17].

### Secondary outcome measurement

The visual analogue scale (VAS) for self-assessment of ocular discomfort will be used. Self-reports on ocular symptoms concomitant with dry eye will be obtained for such conditions as ocular itching, foreign body sensation, burning, pain and dryness as well as for blurred vision, sensation of photophobia, ocular redness and sensation of tearing. Each participant will record a score indicating his or her total level of discomfort on a 100 mm horizontal line.

Tear Film Break-Up Time (TFBUT) and the Schirmer I test with anaesthesia will be used as additional secondary outcome variables. TFBUT is a method for observing tear film stability. Sodium fluorescein (2.5%) will be instilled in both eyes and the tear break-up time (the interval between the last complete blink and the first appearance of a dry spot or disruption in the tear film) will be measured [18]. The Schirmer I test with anaesthesia is a method for checking basic tear secretion. Schirmer test paper (Color Bar™ Eagle Vision, USA) will be inserted on the lateral third of the lower eyelid with the participant's eye closed for five minutes. Each test will be performed by a single ophthalmologist.

Medication Quantification Scale (MQS) and General Assessment of Improvement will also be used as secondary outcome variables. The total frequency and dosage of artificial tears will be checked. At the final visit of each participant, both participant and practitioner will assess improvements in ocular symptoms. 'Excellent' indicates the presence of no symptoms related to dry eye and much improvement in daily life; 'Good' means that a few symptoms related to dry eye are present but that the condition is better than before treatment; 'Fair' means that several symptoms related to dry eye are present but that the condition is a little improved; 'Poor' means that there is no change compared with before treatment; 'Aggravation' means that symptoms are worse than they were before treatment (Table 1).

**Table 1 T1:** Schedule for treatment and outcome measurement

Period	screening										F/U
Visit	1	2	3	4	5	6	7	8	9	10	11
Week		1st			2nd			3rd			Visit10+ 1 week+ 3 days
Informed consent	ν										
Demographic characteristics	ν										
Medical History	ν										
Physical examination	ν										
Random Allocation		ν									
Acupuncture Treatment		ν	ν	ν	ν	ν	ν	ν	ν	ν	
Symptom score	ν	ν	ν	ν	ν	ν	ν	ν	ν	ν	ν
OSDI		ν		ν			ν			ν	ν
Schirmer I test	ν									ν	
TFBUT	ν									ν	
MQS		ν	ν	ν	ν	ν	ν	ν	ν	ν	ν
General assessment (patient/doctor)										ν	
Blinding Assessment		ν									ν
Safety Assessment		ν	ν	ν	ν	ν	ν	ν	ν	ν	ν

OSDI: Ocular Surface Disease Index; TFBUT: Tear Film Break-up Time; MQS: Medication Quantification Scale

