## Methods/Design

This study is a randomised, patient-assessor blinded, sham acupuncture controlled trial. Enrolled participants will be randomly allocated to either a verum acupuncture or a sham acupuncture group and will receive nine sessions of treatment over a three-week period. Participants will be examined for signs and symptoms of dry eye before and after treatment (Figure 1).

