### Sample size and randomisation

We wished to estimate the sample size that would suffice to detect an 18 point difference in the Ocular Surface Disease Index (OSDI) between the verum and control groups. In our previous uncontrolled acupuncture study, the standard deviation of OSDI was estimated to be 19.342 [13]. If we apply a two-sided 5% significance level, 90% power and 10% dropout rate, the calculated required sample size is approximately 21 participants in each group, according to the following equation:

An expert on statistics from KIOM who has no direct contact with the study participants will conduct randomisation of participants. He/she will generate random numbers with block randomisation using the SAS statistical package (Version 9.1.3; SAS institute Inc.). The block size will be concealed from other researchers and the randomisation table will not be available for assessment by anyone else involved in the study.

Opaque sealed envelopes containing serial numbers will be delivered to the clinical trial centre. Before the random assignment, all participants will be informed that they will be allocated to one of two groups. Random allocation will be conducted at visit 2. Random numbers with corresponding participants will be determined in the order of the time of second visit and will be opened by acupuncture practitioners. The allocation result will not be announced to the participants until the last visit of the last randomised participant.

The success of blinding will be assessed at each participant's last visit. Researchers who did not participate in the acupuncture treatment and who are blinded to the allocation results will perform the outcome assessment.

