### Acupuncture treatment protocol

Acupuncture of both groups will be carried out by licensed oriental medicine physicians who have been trained for four years and have at least five years of clinical experience in acupuncture treatment. Acupuncture practitioners will be required to attend a one-day training course on this study.

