### Sham acupuncture group (non-acupuncture point shallow penetration group)

A sham acupuncture point corresponding to each verum acupuncture point was selected. The principle of sham point selection is that the sham point should not be a classical acupuncture point and should, except for points on the rim of the eye, be located close to the verum point. The selected sham points are as follows: both points 2 cm lateral to ST4, 2 cm below ST7, at the parietal eminence of head, 2 cm internal to ST9, 10 cm internal to BL57, 1.5 cm internal to ST36, one point at the left middle point of the bicepsbrachii muscle belly, points at 2 cm, 4 cm, and 6 cm from the Lt. wrist fold, and one point located between the Lt. 3^rd ^and 4^th ^metatarsophalangeal joints. After shallow penetration of the skin at each site with no manipulation for 'de qi,' the needle is left for 20 minutes. Every participant in the sham acupuncture group will be treated three times per week for three weeks.

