### Adverse events

We define adverse events as unfavourable or unintended signs, symptoms or disease occurring after treatment that are not necessarily related to the acupuncture intervention. Acupuncture-related adverse events are defined as local symptoms including bruising and pain for over two weeks at acupuncture points, peripheral neuritis and swelling, redness and itching for over three days, systemic symptoms including dizziness and palpitation, and psychiatric problems including headache for over three days, anxiety or fear for over 60 hours, and hypersensitivity for over three days. In case of serious medical problems, other symptoms could be included in adverse events. In every visit, adverse events will be reported by participants and examined by the practitioner.

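### The practitioner rates the General Assessment of Improvement, a secondary outcome, although the article reserves outcome assessment for blinded researchers who did not treat

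*Protocol article*

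**What the plan says.** The Methods/Design section sets the label: "This study is a randomised, patient-assessor blinded, sham acupuncture controlled trial". The Sample size and randomisation section says what that means for measurement: "Researchers who did not participate in the acupuncture treatment and who are blinded to the allocation results will perform the outcome assessment". The same section says of the random numbers that they "will be opened by acupuncture practitioners".

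The Acupuncture treatment protocol section states who needles: "Acupuncture of both groups will be carried out by licensed oriental medicine physicians". Its closing sentence calls these people practitioners: "Acupuncture practitioners will be required to attend a one-day training course on this study".

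The Secondary outcome measurement section counts the General Assessment of Improvement among the secondary outcomes, with five categories from Excellent to Aggravation, and names two raters: "At the final visit of each participant, both participant and practitioner will assess improvements in ocular symptoms". Table 1 labels the row as patient and doctor and ticks it at visit 10 only.

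On safety, the Adverse events section says that "adverse events will be reported by participants and examined by the practitioner".

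**The concern.** The blinding rule sets two conditions for an outcome assessor: not having treated the participant, and not knowing the allocation. The practitioner appears to meet neither, yet rates a named secondary outcome.

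The scale leaves room for judgement. Good and Fair, for example, are separated by how many symptoms remain and how much better the condition is, with no count or threshold. A therapist who knows which needling was given, and who may expect the verum technique to work, could lean towards the better category in one arm. The Statistical analysis section compares secondary outcomes between groups, and the abstract lists this measure among those used to judge effectiveness. The rating would therefore enter an efficacy comparison in a trial presented as assessor-blinded.

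**Working it through.** No arithmetic applies. The check sets the statements side by side.

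1. **Who may assess outcomes.** Under Sample size and randomisation, only researchers who did not treat and who are blinded. No exception is made for any outcome.

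2. **Is the General Assessment an outcome?** Yes. The Secondary outcome measurement section names it as one, and so does the abstract.

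3. **Who rates it?** The participant and the practitioner. The participant is blinded: the allocation is withheld from participants until the last visit of the last person randomised. The question concerns the second rater only.

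4. **Who is the practitioner?** The treatment section uses the word for those who give the acupuncture, and the randomisation section uses it for those who open the allocation. They are also physicians, so the word doctor in Table 1 fits them. Visit 10 is itself a treatment visit, so the treating practitioner is present when the rating is ticked.

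5. **Could that person be blinded?** No. Apart from opening the allocation, the practitioner carries out two plainly different procedures. Verum uses named points with twisting until a needle sensation is felt. For sham, the article says: "After shallow penetration of the skin at each site with no manipulation for 'de qi,' the needle is left for 20 minutes". The sham sites are also not classical acupuncture points.

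6. **Result.** The practitioner fails both conditions in step 1, so the two sections conflict.

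7. **Reach.**

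| Measure | Who provides it | Touched by this point? |
|---|---|---|
| OSDI (primary) | Participant | No |
| VAS | Participant | No |
| TFBUT, Schirmer I | A single ophthalmologist | No |
| General Assessment, participant | Participant | No |
| General Assessment, practitioner | Practitioner | Yes |

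MQS rests on recorded use of artificial tears. The article does not say who checks it, so nothing is claimed about it here.

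8. **Timing.** The text places the rating at each participant's final visit, but Table 1 ticks visit 10, while the last scheduled visit is visit 11 (follow-up). TFBUT and Schirmer I are ticked at visit 10 and not at visit 11. Which visit is meant therefore decides whether the ophthalmologist is already scheduled.

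**The case against.** **The practitioner may be someone else.** The outcome section does not say acupuncture practitioner, Table 1 says doctor, and the Recruitment section shows that other physicians and ophthalmologists work at the centre. This reading is possible but less likely, given how the article uses the word elsewhere. If it is the intended one, a clarifying phrase settles the matter, but the text still has to change.

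**Acupuncturists cannot be blinded.** True, and no one needs to ask for that. The point concerns who rates an outcome, not who needles.

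**An article condenses the full protocol.** That would excuse an omission. Here the article states who rates, and the statement conflicts with its own rule.

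**The reach is small.** This stands. A reader might infer that the assessor-blinded label fails for the whole trial or that the primary outcome is compromised. The table above shows otherwise.

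**Adverse events.** A reader might also infer that the safety data contradict the blinding rule in the same way, or that the whole between-group safety comparison is exposed. The article does not support that:
- The rule covers outcome assessment, and safety is not listed among the primary or secondary outcomes.
- Events are reported first by blinded participants. The practitioner examines them, but is not said to grade or attribute them.
- Many of the acupuncture-related events are defined by duration, which limits discretion.
- The Statistical analysis section plans no between-group test of safety.

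What remains is narrower: the person who examines adverse events is unblinded, and the assessor-blinded label should not be read as covering safety.

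**Conclusion.** The contradiction holds for the practitioner's half of the General Assessment of Improvement. It affects one of two raters of one secondary outcome and leaves the primary outcome untouched.

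The size and direction of any bias cannot be derived from the article. A shift expressed in categories would only restate whatever rate of over-rating one chose to assume, so none is offered.

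The conclusion assumes that the practitioner who rates is the one who treats, which is the natural but not the only reading. It also assumes that the general blinding rule applies to every listed outcome, since no exception is stated. The ophthalmologist's blinding follows from that same rule but is not stated individually. The point should be corrected, though it does not threaten the trial's main conclusion.

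**What to change.** Choose one of two routes for the General Assessment:

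- **Reassign it.** Have the doctor's rating made at visit 10 by a blinded assessor who did not treat. The ophthalmologist is already scheduled then for TFBUT and Schirmer I; confirm in the text that this person is blinded. Reconcile the final-visit wording with the visit 10 tick in Table 1.
- **Relabel it.** Keep the practitioner's rating, describe it as unblinded, exclude it from efficacy claims, and rely on the participant's rating for this outcome.

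If a separate, blinded doctor was always intended, say so in the outcome section and in Table 1.

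For safety, add one sentence stating that the practitioner who examines adverse events is unblinded and that the assessor-blinded label does not extend to safety. Do not pass adverse-event grading to the ophthalmologist. Verum and sham sites differ, so bruising or redness at needle sites could reveal the allocation to the person measuring TFBUT and Schirmer I. It would also add work at the ten visits (2 to 11) where Table 1 schedules safety assessment, whereas the ophthalmological tests occur only at visits 1 and 10.

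Reassigning costs one form and a few minutes of an assessor already present, provided that visit 10 is confirmed as the time of rating. Relabelling costs only wording. Neither changes treatment or sample size.

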### Statistical analysis

We will conduct analysis on an intention-to-treat basis (significance level p < 0.05) using the SAS statistical package program (ver. 9.1.3). Baseline characteristics will be shown as mean ± standard deviation (SD) for continuous data including age, previous duration of dry eye, OSDI, VAS for self-assessment of ocular discomfort, TFBUT and Schirmer's I test value. As for participants' gender, n (%) of male and female in each group will be shown as baseline characteristics. We will conduct between-group comparision in baseline using two-sample t-test or Wilcoxon rank sum test for continuous data and using Chi-square test or Fisher's exact test for gender composition considering p < 0.05 as statistically significant.

For primary and secondary outcome measures, the mean differences from baseline values to the end of treatment will be compared using two-sample t-test or Wilcoxon rank sum test. If any imbalances in baseline characteristics between groups are encountered, we will conduct ANCOVA (analysis of covariance) using these imbalanced variables as covariates and allocated group as fixed factor.

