## Appendix 1. Inclusion and Exclusion Criteria

### Inclusion Criteria

Patients who have had dry eye syndrome in a single eye or in both eyes (ICD-10: H04.1).

He or she must have both of the conditions below:

• Patients who have been having symptoms such as ocular itching, ocular foreign body sensation, ocular burning, ocular pain, ocular dryness, blurred vision, sensation of photophobia, ocular redness or sensation of tearing

• Patients whose Tear Film Break-Up Time (TFBUT) is below 10 seconds and measured tear amount is below 10 mm/5 sec by the Schirmer I test

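### The change-from-baseline rule set for every secondary outcome cannot be applied to the General Assessment of Improvement, which has no baseline and is itself a rating of change

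*Protocol article*

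**What the plan says.** The Statistical analysis section gives a single rule without exceptions: "For primary and secondary outcome measures, the mean differences from baseline values to the end of treatment will be compared". The test is to be either a t-test for two samples or the rank sum test. The section adds a conditional alternative, which begins "If any imbalances in baseline characteristics between groups are encountered, we will conduct ANCOVA (analysis of covariance". The abstract says instead that all analyses will use ANCOVA.

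Under Secondary outcome measurement, "Medication Quantification Scale (MQS) and General Assessment of Improvement will also be used as secondary outcome variables". On timing, the same section says "At the final visit of each participant, both participant and practitioner will assess improvements in ocular symptoms". The scale has five ordered categories, from *Excellent* to *Aggravation*. Table 1 has one tick in the row that begins "General assessment (patient/doctor", in the visit 10 column. There is none at screening, at visit 2 or at the follow-up visit 11.

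For TFBUT the text says "Sodium fluorescein (2.5%) will be instilled in both eyes". For the Schirmer I test it refers to the participant's eye in the singular. Table 1 places both tests at visits 1 and 10. Appendix 1 admits "Patients who have had dry eye syndrome in a single eye or in both eyes".

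**The concern.** A change from baseline needs two measurements on the same scale. The General Assessment has one, and its categories are themselves comparisons with the state before treatment. A mean difference is also a poor summary of five ordered labels. If the stated rule cannot be executed, someone has to choose another method later, possibly with the data in view. The practitioner's rating deserves particular care, because the section on sample size and randomisation has the acupuncture practitioners open the allocation.

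A second question follows from the same rule. The t-test and the rank sum test assume independent observations, while TFBUT is read in two eyes of one person. The article does not say how two eyes become one observation. If each eye were entered separately, the standard error would be too small.

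**Working it through.** The plan gives no figure of its own on this point, so there is nothing to reproduce first.

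**General Assessment, passages side by side**

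1. The rule covers all secondary outcomes (Statistical analysis).
2. The General Assessment is one of them (Secondary outcome measurement).
3. The rule needs a value at baseline and a value at the end of treatment. Table 1 provides one value, at visit 10.
4. A baseline value could not be collected in any case. *Poor* is defined as no change, and *Aggravation* as worse, relative to the time before treatment. Neither has a meaning before treatment starts.
5. The conditional ANCOVA does not help. It adds covariates for imbalanced baseline variables but supplies no baseline rating, and it models a mean. The abstract's ANCOVA statement has the same limitation.
6. The text puts the rating at the final visit. Table 1 puts it at visit 10, although visit 11 is the last visit. On either reading there is no baseline.

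The rule is therefore not executable for this outcome.

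**TFBUT and Schirmer: what the unit of analysis would do**

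Inputs:
- two-sided 5% level and about 21 participants per group (Sample size and randomisation);
- two eyes per participant (stated for TFBUT only);
- inter-eye correlation r, not given in the article, so assumed from 0.5 to 0.9.

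With n participants per group and variance s² per eye, the variance of a group mean over both eyes is s²(1 + r)/(2n). A test that takes the 2n eyes as independent uses s²/(2n). The true variance is larger by the factor 1 + r, so

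type I error = 2 × [1 − Φ(1.96/√(1 + r))].

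| Assumed r | 1.96/√(1 + r) | Type I error, formula | Simulated, eyes pooled | Simulated, one mean per participant |
|---|---|---|---|---|
| 0.5 | 1.600 | 0.110 | 0.111 | 0.050 |
| 0.7 | 1.503 | 0.133 | 0.136 | 0.050 |
| 0.8 | 1.461 | 0.144 | 0.148 | 0.050 |
| 0.9 | 1.422 | 0.155 | 0.161 | 0.049 |

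The simulation used t-tests, 21 participants per group and 20,000 runs. One value per participant keeps the error at its nominal level whatever the correlation.

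**ANCOVA on the visit 1 value**

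A test on raw change fixes the coefficient of the baseline at 1. ANCOVA estimates it by least squares, so its residual variance is no larger, apart from the one degree of freedom spent on the slope. The visit 1 values of both tests are already collected.

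**The case against.** The strongest objection concerns the eyes. A reader might infer from the both-eyes wording that the trial will count eyes as independent units, and so will report false-positive support for acupuncture on both objective tests. The article does not support that:

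- Nothing says eyes are the unit of analysis. Randomisation and sample size are per participant, and TFBUT and Schirmer are listed as baseline characteristics beside age and disease duration.
- Both-eye measurement is stated for TFBUT only.
- How two eyes become one value is a detail that an article may leave to the full protocol or the analysis plan.
- With one value per participant the stated tests are valid.
- The inflated error is two-sided. By symmetry about half of it, 0.055 to 0.078 against a nominal 0.025, would favour acupuncture.

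All of this stands. The table above shows what a wrong choice would cost; it does not show that the choice has been made. Preferring ANCOVA to a test on change is likewise an improvement in precision, not the correction of an invalid method.

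On the General Assessment, it can be said that the Wilcoxon test is already named and could simply be run on the ratings, and that no bias or loss of power has been shown. That is fair, and it keeps the point small. It does not remove it: the article does not leave the method open, but states one that cannot be followed.

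**Conclusion.** The point holds for the General Assessment. As written, the change-from-baseline rule cannot be applied to it, and nothing else in the article repairs this. The conclusion rests only on the article's text and Table 1, with no numerical assumption.

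For TFBUT and Schirmer no error is shown. The 0.11-0.16 range depends on eyes being pooled, which the article does not say, and on assumed correlations of 0.5-0.9. For Schirmer it depends also on testing both eyes, which is not stated. Fixing one value per participant is a clarification, and ANCOVA on the visit 1 value is a low-cost improvement.

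Severity is minor. Only secondary outcomes are affected; the primary outcome, OSDI, is one score per participant and has a baseline at visit 2.

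**What to change.** 1. Exempt the General Assessment of Improvement from the change-from-baseline rule. Compare the post-treatment categories directly between groups by the Wilcoxon rank sum test already named, or by a proportional-odds model. Analyse and report the patient and practitioner ratings separately.
2. Reconcile the final-visit wording under Secondary outcome measurement with the visit 10 tick in Table 1.
3. For TFBUT and Schirmer, define one value per participant before unblinding and use the same eyes at visits 1 and 10. The mean of the eyes that met the entry criteria at screening is one workable choice. It avoids averaging in an unaffected eye: if that eye does not change, a change of d in the other eye becomes (d + 0)/2 = d/2. Analyse the visit 10 value by ANCOVA with the visit 1 value as covariate, whether or not the groups look balanced. State whether Schirmer is measured in one eye or both.

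The cost is a few sentences of analysis wording. No added visits, measurements or participants are needed. If pooling of eyes had been intended, the TFBUT interval would become wider, and correctly so.

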**Methods/Design:**

A randomised, patient-assessor blinded, sham (non-acupuncture point, shallow acupuncture) controlled study was established. Participants allocated to verum acupuncture and sham acupuncture groups will be treated three times weekly for three weeks for a total of nine sessions per participant. Seventeen points (GV23; bilateral BL2, GB4, TE23, Ex1 (Taiyang), ST1 and GB20; and left SP3, LU9, LU10 and HT8 for men, right for women) have been selected for the verum acupuncture; for the sham acupuncture, points have been selected that do not coincide with a classical acupuncture point and that are located close to the verum points, except in the case of the rim of the eye. Ocular surface disease index, tear film breakup time, the Schirmer I test, medication quantification scale and general assessment of improvement will be used as outcome variables for evaluating the effectiveness of acupuncture. Safety will also be assessed at every visit. Primary and secondary outcomes will be assessed four weeks after screening. All statistical analyses will be performed using analysis of covariance.

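### The abstract promises ANCOVA throughout, but the analysis section uses it only after a baseline imbalance; this costs power and leaves it to chance whether baseline OSDI is a covariate

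*Protocol article*

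**What the plan says.** The protocol article describes the main analysis in two places.

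- Abstract, Methods/Design: "All statistical analyses will be performed using analysis of covariance". No condition is attached.
- Statistical analysis: for primary and secondary outcomes, "the mean differences from baseline values to the end of treatment will be compared using two-sample t-test or Wilcoxon rank sum test". ANCOVA comes next, conditionally: "If any imbalances in baseline characteristics between groups are encountered, we will conduct ANCOVA (analysis of covariance) using these imbalanced variables as covariates", with allocated group as the fixed factor.

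The same section compares seven baseline variables between groups (age, duration of dry eye, OSDI, VAS, TFBUT, Schirmer and gender) and takes p < 0.05 as significant. It does not say in so many words that this threshold defines an imbalance, but no other criterion is offered. Nothing commits the trial to baseline OSDI as a covariate whatever the data show.

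The Sample size section aims to "detect an 18 point difference in the Ocular Surface Disease Index (OSDI) between the verum and control groups", says that "the standard deviation of OSDI was estimated to be 19.342", and applies a "two-sided 5% significance level, 90% power and 10% dropout rate" to reach about 21 per group. It does not say whether the SD is that of a single score or of change, and it does not tie the calculation to either analysis.

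**The concern.** The article names two different main analyses, so a reader cannot tell which p-value is primary. This is a conflict within the published text, not a detail left to a statistical analysis plan.

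The conditional rule is also a poor choice. After proper randomisation, a baseline significance test can flag only chance differences, and it says nothing about whether a variable predicts the outcome. Baseline OSDI is the natural predictor of final OSDI whether or not it differs between groups. Under the rule it is left out of most trials, while a weak predictor may enter because it happened to be flagged. In a trial of about 42 participants, the precision given up could decide the result.

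**Working it through.** **Inputs from the Sample size section.** Difference 18, SD 19.342, two-sided 5%, 90% power, 10% dropout, 21 per group; 21 × 0.9 = 18.9, so about 19 evaluable. **Assumption:** r, the correlation between baseline and end-of-treatment OSDI, is not given; range 0.3 to 0.8. Equal SDs at the two times are also assumed.

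**The plan's own figure.** n = 2(1.960 + 1.282)² × (19.342/18)² = 24.27, so 25 per group before dropout and 28 after (25/0.9 = 27.8). The stated 21 is not reproduced. At 80% power the same formula gives 18.13, and 18.13/0.9 = 20.1, so 21. That is a separate sample-size question. It matters here only because it leaves less power to spare.

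**Efficiency.** The variance of a change score is 2·SD²(1 − r). The ANCOVA residual variance is SD²(1 − r²). Their ratio is (1 + r)/2, or 0.65, 0.75, 0.85 and 0.90 at r = 0.3, 0.5, 0.7 and 0.8. The table gives noncentral-t power for 18 points with 19 per group (36 degrees of freedom for change, 35 for ANCOVA).

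| r | 19.342 = single-score SD: SD of change / ANCOVA residual SD | Power, change v ANCOVA | 19.342 = SD of change: ANCOVA residual SD | Power, change v ANCOVA |
|---|---|---|---|---|
| 0.3 | 22.9 / 18.5 | 65.5% v 83.2% | 15.6 | 79.7% v 93.3% |
| 0.5 | 19.3 / 16.8 | 79.7% v 89.6% | 16.8 | 79.7% v 89.6% |
| 0.7 | 15.0 / 13.8 | 95.0% v 97.4% | 17.8 | 79.7% v 85.7% |
| 0.8 | 12.2 / 11.6 | 99.3% v 99.6% | 18.3 | 79.7% v 83.6% |

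At r = 0.5 the two readings coincide, because 2(1 − r) = 1.

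**Does the conditional rule recover the loss?** Simulation with 40,000 trials, 19 per group, r = 0.5, SD of change 19.342, and baseline OSDI at p < 0.05 as the only trigger gave power of 79.8% for the change score, 80.6% for the conditional rule and 88.7% for ANCOVA always. It recovers almost nothing. The simulated 88.7% is slightly below the formula's 89.6%, which ignores chance baseline imbalance.

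**How large a difference goes unflagged?** With a single-score SD and a p < 0.05 trigger at 21 per group: t(0.975, 40) × 19.342 × √(2/21) = 2.021 × 5.969 = 12.06 points, or 67% of the 18-point target. Subtracting baseline over-corrects for a baseline difference D by (1 − r)·D. For D = 12.06 that is 8.4, 6.0, 3.6 and 2.4 points at r = 0.3, 0.5, 0.7 and 0.8.

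**Chance selection of covariates.** If the seven baseline tests were independent, at least one would be flagged in 1 − 0.95⁷ = 30% of properly randomised trials. Baseline OSDI itself would be flagged in about 5%.

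**Error rates under the null.** Simulated at 21 per group, single-score SD:
- Overall, the change score rejects about 5.0% and the conditional rule 4.1 to 4.6% (r from 0.3 to 0.7).
- An unflagged baseline difference of 8 to 12 points occurs in about 12% of trials. In those, the change-score test rejects a true null 7 to 10% of the time, against about 5% for ANCOVA.
- In the roughly 82% of trials with a difference below 8 points, the change score rejects only 3 to 4%, so the overall rate balances out.

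**The case against.** The strongest reply is that the rule does no harm to the error rate. That stands. A reader might infer from a data-chosen test that the false-positive rate is inflated, or read the 7 to 10% as the trial's error rate. Neither is supported. The route depends on baseline data, not outcomes; the overall rate is 4 to 5%; and the higher figure applies only within the 12% of trials described.

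The change score is also unbiased over randomisations, and it does use baseline. The shift of (1 − r)·D is conditional on the imbalance observed, and it is an over-correction. It would be wrong to call the estimate biased without that condition, or to say that baseline is ignored.

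The size depends on two things the article does not give: r, and the meaning of 19.342. With a single-score SD and r of 0.7 or more, the gain is 2 points of power or less. The 12-point figure also needs the p < 0.05 trigger, which is inferred from the preceding text. If imbalance is judged some other way, the figure falls away and the rule is undefined.

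Two further readings go beyond the text. The article does not say that the smaller of the t-test and Wilcoxon p-values will be taken. It also does not say that participants without a visit-10 score will be excluded. The choice between tests and the handling of missing values may properly sit in the fuller plan.

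None of this removes the contradiction, or gives a reason to prefer the conditional rule.

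**Conclusion.** The concern holds in this form: the abstract and the Statistical analysis section contradict each other on the main analysis, and the version in the analysis section is the weaker one. The loss is power, together with error conditional on the observed baseline difference; overall type I error is sound.

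At r = 0.5, power is about 80% instead of about 90% under either reading of the SD. Over r = 0.3 to 0.8 the loss runs from about 18 points to under 1 if 19.342 is a single-score SD, and from about 14 points to about 4 if it is the SD of change. These figures rest on the assumed r, equal SDs at the two times and 19 evaluable per group. The contradiction rests on no assumption and should be settled before outcome data are seen.

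**What to change.** 1. State one primary analysis: ANCOVA of end-of-treatment (visit 10) OSDI on allocated group, with baseline (visit 2) OSDI as covariate, whatever the baseline comparisons show. Report the adjusted difference with its 95% confidence interval.
2. Do the same for the continuous secondary outcomes, each with its own baseline value.
3. Delete the imbalance trigger. Baseline tables may stay as description.
4. Keep the t-test or Wilcoxon test on change as a sensitivity analysis.
5. Make the abstract and the Statistical analysis section say the same thing.

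The schedule in Table 1 already collects OSDI at visits 2 and 10, so no new data are needed. The cost is wording and one degree of freedom for the covariate.
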